### 3.6. Recruitment

As the detailed sample size calculation (see Section 4.4) already indicates to have an effect with a small sample size of seven persons, the aim is in consequence to gain 10 female and male patients of approximately the same age for the study estimate to conduct first rough analyses.

Further, based on the number of patients per year in our clinical setting, it seems reasonable to win enough patients within 2 years. We estimate an average of one patient a week, yielding a total of 50 patients a year so that we will have enrolled a total of around 100 patients after 2 years. The recruitment will be conducted by the department of internal medicine of the Lindenhofgruppe and its associated General practitioners. Due to the common characteristics of patients with type 2 diabetes mellitus we expect to mainly recruit patients above 50 years of age and slightly more male than female patients. Furthermore, the obstetrics department of Inselspital Berne with its Patients with a potential indication of metformin due to PCOS will also be included.

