### 3.4. Eligibility Criteria

#### 3.4.1. Inclusion Criteria

Patients (male or female) older than 18 years with type 2 diabetes mellitus and an indication for metformin according to the American Diabetes Association, starting a new metformin treatment or are pausing treatment for example due to a further medical investigation for at least seven days. The main marker will be fasting plasma glucose levels of≥ 7.0mmol/L and/or HbA1c ≥ 6.5% [56].

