#### 3.4.2. Exclusion Criteria

Patients under 18 years of age.Clinically significant concomitant disease (e.g., advanced renal failure, hepatic dysfunction, neoplasia).Significant musculoskeletal disease.Active infection during sample collection.Immunosuppressive medical therapy.Hormonal/steroid treatment.Pregnancy.Psychiatric disease and known social-behavior-altering medication (e.g., antipsychotic medication).Known or suspected malcompliance, drug or alcohol abuse.Inability to follow the procedures of the study, e.g., due to insufficient language skills, severe dementia.Life expectancy less than 6 months.Poor tolerability to metformin treatment with following treatment discontinuation within duration of follow-up.Pharmaceutical treatment with insulin or another pharmaceutical with a known strong effect on blood sugar levels.

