Progesterone metabolites: 17-Hydroxypregnanolon, Pregnanediol, Pregnanetriol, 11-Oxo-Pregnanetriol Aldosterone-Metabolites: Tetrahydroaldosterone.

Corticosterone metabolites: TetrahydroDOC, Tetrahydrodehydrocorticosteron, Tetrahydrocorticosteron, 5a-Tetrahydrocorticosteron, 18-Hydroxy-tetrahydrocompound A, Cortisone.

Cortisone metabolites: Tetrahydrocortisone, a-Cortolon, b-Cortolon, 20a-Dihydrocortison, 20b-Dihydrocortison.

Cortisol metabolites: Cortisol, Tetrahydrocortisol, 5a-Tetrahydrocortisol, a-Cortol, b-Cortol, 20a-Dihydrocortisol, 6b-Hydroxycortisol, 18-Hydroxycortisol.

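### With no control group, barring only active infection at sampling is too narrow: recovery from another acute illness between baseline and week 12 could be read as a metformin effect

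*Protocol article*

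**What the plan says.** **Source of patients.** Section 3.6: "The recruitment will be conducted by the department of internal medicine of the Lindenhofgruppe and its associated General practitioners". The same section adds that "the obstetrics department of Inselspital Berne with its Patients with a potential indication of metformin due to PCOS will also be included".

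**Entry.** Section 3.4.1 requires type 2 diabetes with an indication for metformin, in patients "starting a new metformin treatment or are pausing treatment for example due to a further medical investigation for at least seven days".

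**Exclusions bearing on the patient's state.** Section 3.4.2 lists "Active infection during sample collection", which is the only criterion tied to the time of sampling. It also lists "Clinically significant concomitant disease (e.g., advanced renal failure, hepatic dysfunction, neoplasia" (an open list of examples), "Hormonal/steroid treatment", immunosuppressive therapy, and insulin or other drugs with a strong effect on blood sugar.

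**Timing and analysis.** Urine and AQ are obtained once before metformin starts and once after 12 weeks (Sections 3.5, 4.1 and 4.2). Section 5 compares the two by two-sided paired t-tests with Bonferroni correction, or by Wilcoxon tests. Section 6 concedes that a placebo-controlled crossover would be the best design but calls it impracticable.

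**Endpoints most exposed.** Section 4.1 names eight compounds under "Cortisol metabolites: Cortisol, Tetrahydrocortisol, 5a-Tetrahydrocortisol, a-Cortol, b-Cortol, 20a-Dihydrocortisol, 6b-Hydroxycortisol, 18-Hydroxycortisol", five under cortisone metabolites, and adrenal androgens such as dehydroepiandrosterone.

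**The concern.** In an uncontrolled before-after comparison, any systematic change in the patients' condition between the two visits is attributed to the treatment. Illness is likelier at the contact that leads to a prescription than at a visit fixed 12 weeks later. If some patients give their baseline urine while acutely unwell and their second sample after recovery, the change is likely to run largely one way. It would not average out, and a larger sample would only make it more significant.

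The plan already accepts that the patient's condition at sampling matters, since it excludes active infection. Other acute states, and the setting in which a sample is taken, are not addressed at that point. The adrenal metabolites would be affected first. If AQ answers moved too, the steroid–AQ correlation sought as a secondary endpoint could be affected as well.

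**Working it through.** **1. The plan's own figure.** Section 4.4 takes testosterone from 2.7 ± 0.3 to 2.0 ± 0.2 nmol/L, alpha 0.001136 and 80% power, and states n = 7. That alpha equals 0.05/44 (the fraction is printed as 0.005/44). With d = 0.7/√((0.3² + 0.2²)/2) = 2.746, a two-sided paired t-test by noncentral t needs n = 7, so the figure reproduces. One quarter of that effect, d = 0.686, needs 41, against a stated figure of around 45. These figures fix the alpha and the sample sizes used below; they do not themselves bear on the concern.

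**2. Is a non-infectious acute illness at baseline barred?**

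| Provision | Effect |
|---|---|
| Active infection at sampling (3.4.2) | Bars infection only |
| Clinically significant concomitant disease (3.4.2) | Could be read to cover an acute illness; the examples are renal failure, hepatic dysfunction and neoplasia |
| Steroids, immunosuppression, insulin (3.4.2) | Remove some hospital patients, not all |
| Type 2 diabetes with indication (3.4.1) | Fixes the diagnosis, not the condition at sampling |
| Reference values, optional matching to healthy subjects (5) | The matching is aimed at age bias; neither corrects a change within a patient |

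So it is not clearly barred.

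**3. What would it do?** The article gives neither the share affected nor the size of the fall, so both are assumed. Let a share p have a baseline raised by D, in SDs of the paired change, with full recovery by week 12 and no drug effect. The standardised mean change is

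b = pD / √(1 + p(1 − p)D²),

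and the rejection probability follows from the noncentral t with noncentrality b√n at two-sided alpha 0.05/44. For p = 0.3 and D = 1: b = 0.3/√1.21 = 0.27. At n = 45 the noncentrality is 1.83 against a critical value of 3.48, which gives 6.3%.

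| Share p | Fall D | b | n = 45 | n = 100 |
|---|---|---|---|---|
| 10% | 0.5 SD | 0.05 | 0.2% | 0.3% |
| 10% | 1 SD | 0.10 | 0.4% | 1.0% |
| 20% | 0.5 SD | 0.10 | 0.4% | 1.1% |
| 20% | 1 SD | 0.19 | 2% | 7% |
| 30% | 1 SD | 0.27 | 6% | 27% |
| 30% | 1.5 SD | 0.37 | 18% | 64% |
| 50% | 1 SD | 0.45 | 33% | 86% |

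The nominal rate is 0.1% per metabolite. A simulation at n = 45 with a fixed number of affected patients (9, 14 and 22 of 45) and D = 1 gave 1.4%, 5.5% and 29%, in line with the 20%, 30% and 50% rows.

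**4. Estimates as well as tests.** Section 5 also plans effect sizes with 95% intervals, which Bonferroni does not protect. A shift of 0.27 is 0.27/0.686, or about 40%, of the effect on which the figure of around 45 rests.

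**The case against.** **The acute baseline is an inference.** Section 3.6 names a department and general practices, not wards or admissions, and the abstract speaks of healthy adults with a new indication. This stands. A reader might infer that acutely ill inpatients will be enrolled; the documents do not say so. They only leave it possible.

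**The work-up wording does not reach new starters.** A reader might take "pausing treatment for example due to a further medical investigation for at least seven days" to mean that patients under investigation are enrolled generally. The phrase gives a reason for pausing metformin and describes only patients who pause. An investigation is also not an acute illness. This stands.

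**A single raised glucose is not enough for entry.** Section 3.4.1 requires type 2 diabetes with an indication; the glucose and HbA1c values are its main marker. A reading in which stress-raised glucose alone admits a patient is not supported.

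**Other exclusions help.** The concomitant-disease list is open, and the steroid, immunosuppression and insulin criteria remove some hospital patients. This stands in part: none of them clearly covers a short non-infectious illness at the time of sampling.

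**The AQ half is weak.** Section 3.2.2 presents the AQ as assessing individual traits. This stands, although Section 6 hopes to record significant changes in it.

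**The size is all assumption.** With 10% affected, the false-positive rate stays near nominal. This stands, and the range is reported for that reason.

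**The missing control is conceded, and an article may leave sampling conditions to the full protocol.** Both are fair. The article does, however, set a sampling-time rule, and the point is that the rule as written is narrow for this design.

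**Conclusion.** The point holds as a design improvement. The rule on patients' condition at sampling covers infection only, while the analysis has no means of separating recovery from drug effect. Section 3.6 makes an acute baseline possible; it does not make it likely or frequent.

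The consequence ranges from negligible (0.2–0.4% per affected metabolite with 45 patients if 10% are affected) to serious (33% with 45 and 86% with 100 if half are affected by 1 SD). The documents do not show where in that range the trial would fall. The calculation assumes full recovery by week 12, one direction of change, and normally distributed paired differences apart from the shift.

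The conclusion is firmest for cortisol, cortisone and other adrenal metabolites. It is weaker for the AQ and for the steroid–AQ correlation. It would be wrong to state that illness recovery will appear as a metformin effect; it could, and without a record of setting it could not be examined afterwards.

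**What to change.** 1. In Section 3.4.2, widen the sampling-time criterion from active infection to acute illness or inpatient admission at sample collection.
2. Record the setting (inpatient or outpatient) and any acute illness at both visits.
3. If such patients are kept, add a pre/post analysis restricted to pairs in which both urine samples and both AQs were taken as a stable outpatient, and report it beside the analysis of all pairs.

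Metformin treatment and the 12-week follow-up are untouched. Re-sampling after recovery is not proposed, because it would move follow-up off the fixed 12 weeks.

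**Cost.** One changed line in the criteria, two entries on the form at each visit and one added analysis. Some hospital recruits would be lost or left out of the restricted analysis. The projected enrolment of around 100 against the proposed 45 absorbs part of this, but not freely, since the planned analyses by age, sex and menopausal status draw on the same margin.

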## 4. Data Collection Methods

### 4.1. Steroid Measurement Procedures

Analysis of urinary steroids will be conducted via gas chromatography–mass spectrometry. Urine samples shall be taken prior to treatment start and after 12 weeks of treatment (gold standard: 15 mL from a 24 h urine collection). Urine sample preparation comprises pre-extraction, enzymatic hydrolysis, extraction from the hydrolysis mixture, derivatization and gel filtration. The recovery standard will be prepared by adding 2.5 µg of medroxyprogesterone to 1.5 mL of urine. The sample will be extracted on a Sep-Pak C18 column (Waters Corp., Milford, MA, USA), dried, reconstituted in a 0.1 M acetate buffer, pH 4.6, and hydrolyzed with a powdered Helix pomatia enzyme (12.5 mg; Sigma Chemical Co., St. Louis, MI, USA) and 12.5 µL of β-glucuronidase/arylsulfatase liquid enzyme (Roche Diagnostics, Rotkreuz, Switzerland). The resulting free steroids will be extracted on a Sep-Pak C18 cartridge. A mixture of internal standards (2.5 µg each of 5α-androstane-3α, 17α-diol, stigmasterol, and cholesterol butyrate, and 0.15 µg of 3β5β-tetrahydroaldosterone) will be added to this extract, and the sample will be derivatized to form the methyloxime-trimethylsilylethers. Analyses will be performed on a Hewlett Packard gas chromatograph 6890 (Hewlett Packard, Palo Alto, CA, USA) with a mass selective detector 5973 by selective ion monitoring (SIM). One characteristic ion will be chosen for each compound measured. The derivatized samples will be analyzed during a temperature-programmed run (210–265 °C) over a 35 min period. The calibration standard consists of a steroid mixture containing known quantities of all the steroid metabolites to be measured. Responses and retention times will be recorded regularly. In each case, the ion peak will be quantified against the internal stigmasterol standard. All procedures will be performed as described several times by us and others [16,18,58,59,60].

The following metabolites shall be measured as described above [15,16]:

Androgen metabolites: Androsterone, Etiocholanolone, Androstenediol, 11-Oxoetiocholanolone, 11β-Hydroxyandrosterone, 11β-Hydroxyetiocholanolone, Dehydroepiandrosterone, 5-Androstene-3β,17β-diol, 16α-Hydroxydehydroepiandrosterone, 5-Androstene-3β,16α,17β-triol, 5-Pregnene-3β, 16α,17β-triol, Testosterone, 5α-Dihydrotestosterone

Estrogen metabolites: Estriol, 17b-Estradiol.

Progesterone metabolites: 17-Hydroxypregnanolon, Pregnanediol, Pregnanetriol, 11-Oxo-Pregnanetriol Aldosterone-Metabolites: Tetrahydroaldosterone.

Corticosterone metabolites: TetrahydroDOC, Tetrahydrodehydrocorticosteron, Tetrahydrocorticosteron, 5a-Tetrahydrocorticosteron, 18-Hydroxy-tetrahydrocompound A, Cortisone.

Cortisone metabolites: Tetrahydrocortisone, a-Cortolon, b-Cortolon, 20a-Dihydrocortison, 20b-Dihydrocortison.

Cortisol metabolites: Cortisol, Tetrahydrocortisol, 5a-Tetrahydrocortisol, a-Cortol, b-Cortol, 20a-Dihydrocortisol, 6b-Hydroxycortisol, 18-Hydroxycortisol.

### 4.2. Social Behavior Measurement Methods

In order to measure social behavioral changes related to typical behaviors of autism and expand the idea of autism being related to steroid hormone levels, we will be conducting an autism questionnaire prior to and after 12 weeks of treatment. The Autism Spectrum Quotient (AQ) is a questionnaire published in 2001 by Simon Baron-Cohen and his colleagues at the Autism Research Center in Cambridge, UK [52,53,54]. As later research by this group was yielding to steroid hormones and due to its simplicity, we consider this questionnaire as the right choice. Consisting of 50 questions, the aim is to investigate whether adults of average intelligence have traits of autistic behavior. We will analyze the questionnaire according to the guidelines developed by Baron-Cohen et al., 2001.

### 4.3. Data Collection, Management and Retention

Data will be anonymized and stored in a pseudonymized manner. For females before menopause, the day of the menstrual cycle will be reported for further analyses. Personal data including ethnicity will be entered into a separate Excel file with restricted access only by the core staff of the study. Collection and management of the clinical trial data will be done using an electronic data capture system (Red Cap Cloud). Source data will be kept under lock and key. Password protection ensures that only authorized persons can enter the system to view, add or edit data according to their permissions. The complete study dataset is exported and transferred to the investigators as well as to the study statistician through a secured channel. Data will be archived at the Lindenhofspital. Independently from investigators, regulatory authorities can audit this trial. Direct access to source documents will be permitted for purposes of monitoring, audits and inspections. All involved parties must keep the participant’s data strictly confidential. Any results of this study will be published in an anonymized manner. The study protocol and dataset shall be accessible to any regulatory authority after publication for at least 10 years.

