## Abstract

Background: Social behavior is mediated by steroid hormones, whereby various lines of evidence indicate that metformin might improve the symptoms of social withdrawal. This directly yields to the aim of the study to correlate the impact of metformin treatment on the potential alterations in steroid hormone homeostasis, which is ultimately impacting social behavior. Therefore, urinary samples of patients before and after treatment with metformin will be correlated to social behavior to elucidate potential changes in steroid hormone profiles and social behavior. Material and Methods: An observational study in healthy adults with a new indication for metformin. Steroid hormone analysis, including the most prominent androgen, estrogen, progesterone, aldosterone, corticosterone, cortisone and cortisol metabolites analyzed with gas chromatography–mass spectrometry and a questionnaire on social behavior (Autism Spectrum Questionnaire (AQ)) will be administered prior to and after around a 12-week phase of metformin treatment. Discussion: It is likely that due to different pathophysiological mechanisms such as an effect on the respiratory chain in mitochondria or via AMP-activated protein kinase, a general alteration of steroid hormone levels can be detected prior to post treatment. The encompassing measurement of steroid hormones shall give hints concerning the involvement of specific cascades yielding potential pharmacological targets for future research.

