### 3.3. Endpoints

#### 3.3.1. Primary Research Endpoint

Changes in steroid hormone profiles of interest (see below) prior to metformin treatment start and after 12 weeks of treatment.

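### Urine samples from premenopausal women are not matched on cycle phase, which costs precision for the progesterone and estrogen metabolites in that stratum

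*Protocol article*

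**What the plan says.** All references are to the protocol article.

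- **Sampling.** Section 4.1: "Urine samples shall be taken prior to treatment start and after 12 weeks of treatment". The abstract is looser: "prior to and after around a 12-week phase of metformin treatment". Neither sets a condition on cycle phase.
- **Cycle day.** Section 4.3: "For females before menopause, the day of the menstrual cycle will be reported for further analyses". It is recorded, and its use is left open.
- **Endpoint.** Section 3.3.1: "Changes in steroid hormone profiles of interest (see below) prior to metformin treatment start and after 12 weeks of treatment".
- **Panel.** Section 4.1 lists "Progesterone metabolites: 17-Hydroxypregnanolon, Pregnanediol, Pregnanetriol" and "Estrogen metabolites: Estriol, 17b-Estradiol" among the analytes.
- **Analysis.** Section 5 tests each metabolite with a paired t-test or a Wilcoxon test, Bonferroni-corrected in the t-test case. It analyses women before and after menopause separately. Cycle day appears in none of these analyses.
- **Who enrols.** Section 3.6 expects mainly patients above 50 and slightly more men than women, and adds an obstetrics department: "Patients with a potential indication of metformin due to PCOS will also be included". No number of premenopausal women is given. Section 3.4.2 excludes hormonal treatment.
- **Control.** Section 6 says that a placebo-controlled crossover would be optimal but is not practicable.

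**The concern.** The primary comparison is a within-woman difference between two urine samples. If one sample falls in the follicular phase and the other in the luteal phase, the difference in pregnanediol, 17-hydroxypregnanolone, pregnanetriol and the two estrogens contains a cycle component on top of any metformin effect. There is no control group from which that component could be estimated.

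Separate analysis by menopausal status deals with differences between women. It does nothing about a change of phase within a woman. Because hormonal treatment is excluded, the cycles of these women would not be expected to be suppressed. Recording the cycle day shows that the authors saw the issue, but a recorded day cannot re-time a sample already taken. At stake is whether the premenopausal analysis, which the plan commits to, has useful precision for these metabolites.

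**Working it through.** **1. The plan's own sample size.** Section 4.4 gives testosterone 2.7 ± 0.3 falling to 2.0 ± 0.2 nmol/L, 44 metabolites, 80% power, n = 7, and around 45 at one-fourth of the effect size. The per-test alpha of 0.001136 equals 0.05/44 (the printed 0.005/44 would be 0.000114). I use 0.001136. The pre/post correlation is not given; I assume 0.5.

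- SD of the difference = √(0.3² + 0.2² − 2 × 0.5 × 0.3 × 0.2) = √0.07 = 0.265
- Standardised effect = 0.7/0.265 = 2.65; one-fourth of it = 0.66
- Exact noncentral-t, two-sided paired test: n = 8 and n = 44; power at n = 45 is 82%

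A correlation of 0 gives 10 and 77; 0.6 gives 7 and 38. The stated 7 and 45 are therefore reproduced closely, by a calculation with no term for cycle variation.

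**2. Alignment at day 84.** For cycle length L, the shift is the distance from 84 to the nearest multiple of L. If the luteal phase lasts 14 days and the baseline day is arbitrary (both assumed), the chance of different phases for the cycles below is 2 × shift/L.

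| L (days) | Shift (days) | Chance of different phases |
|---|---|---|
| 26 | 6 | 12/26 = 46% |
| 28 | 0 | 0% |
| 30 | 6 | 12/30 = 40% |
| 32 | 12 | 24/32 = 75% |
| 35 | 14 | 28/35 = 80% |

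**3. Share of discordant pairs in a group** (Monte Carlo, all inputs assumed).

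| Cycle length | SD of the 84-day interval | Discordant |
|---|---|---|
| exactly 28 days | 0 | 0% |
| exactly 28 days | 3 days | 17% |
| exactly 28 days | 7 days | 38% |
| mean 29, SD 2 between and 2 within women | 0 to 3 days | 39% to 42% |
| longer or more variable | 5 days | about 49% to 51% |

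In each scenario the luteal share was practically the same at both visits, so switches in the two directions balance.

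**4. Cost in power.** Let p be the discordant share and q the phase shift in units of the cycle-free SD of the difference (q is assumed; the documents give no figure). With balanced directions the variance is multiplied by 1 + p·q². For p = 0.40 and q = 2 this is 1 + 0.40 × 4 = 2.6, so the SD is multiplied by 1.61 and the standardised effect falls from 0.66 to 0.41.

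| p | q | N for 80% power | Power at n = 45 |
|---|---|---|---|
| 0 | – | 44 | 82% |
| 0.15 | 1 / 2 / 3 | 50 / 67 / 96 | 74 / 52 / 30% |
| 0.40 | 1 / 2 / 3 | 59 / 105 / 182 | 61 / 25 / 10% |
| 0.50 | 1 / 2 / 3 | 63 / 121 / 217 | 56 / 20 / 7% |

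The n = 45 column is a benchmark only, because 45 is the whole planned sample. The premenopausal stratum will be smaller and its power lower throughout.

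**5. False positives.** I simulated the paired t-test under no drug effect, with 40% discordant pairs, shifts of ±1.1 or ±2.3 log units, residual SD 0.4 and n = 6, 10 or 15 (all assumed). Rejection was about 3.5% to 5.1% at alpha 0.05 and about 0.0003 to 0.0010 at 0.001136. The error rate is not inflated.

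**The case against.** The strongest case on the other side has four parts.

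- **An article condenses.** The use of cycle day may be set out in an analysis plan that is not shown. That stands for the analysis, but less so for sampling: the article states both the sampling times and what is done with cycle day, and no analysis plan can change the phase of urine already collected.
- **The scope is small.** Most patients are expected to be above 50, the sample leans male, Section 3.4.1 asks for type 2 diabetes, and five of the roughly 39 listed metabolites are in question. Separate analysis keeps the noise out of the postmenopausal results. All of this stands and limits the weight of the point. The PCOS patients in Section 3.6 mean that the stratum need not be negligible, but its size is unknown.
- **Recorded cycle day allows some repair.** Discordant pairs can be identified and set aside in a sensitivity analysis. That stands, although it spends sample size in a small stratum and is not currently specified.
- **Matching helps least in irregular cycles**, which may be common in PCOS. This also stands.

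A reader might infer that phase mismatch will be taken for a drug effect, or that the artefact is many times the planned effect because one out-of-phase pair can move pregnanediol severalfold. Neither is supported. With arbitrary baseline days the switches go both ways, and the standard error of the paired test carries the added variance. Setting one pair's change against a group mean compares unlike things. The one-fourth effect in Section 4.4 is a standardised effect illustrated with androgen-type metabolites, and the documents give no phase difference for pregnanediol. A systematic shift would need a pattern in when samples are taken, and the documents show none.

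**Conclusion.** The point holds as a minor design improvement. The plan ties neither urine sample to cycle phase and specifies no use for the recorded day, so in the premenopausal stratum the paired differences for the progesterone and estrogen metabolites carry avoidable variance. The size depends on inputs that the documents do not give: the discordant share, the phase shift relative to the cycle-free SD, and the pre/post correlation. Over the ranges shown, the required number rises by anything from about one-seventh (44 to 50) to about fivefold (44 to 217). The conclusion concerns power in a minority stratum for a few metabolites. It does not call into question the type I error of the study or the results in men and postmenopausal women.

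**What to change.** - **Sections 4.1 and 4.3.** In women with regular cycles, collect the follow-up urine on the first date from week 12 that falls in the same cycle phase as baseline, for example within 3 days of the baseline cycle day. Record the actual interval. The baseline sample and treatment start do not change.
- **Section 5.** Where cycles are too irregular to match, keep the pair in the primary test. Prespecify a sensitivity analysis of the progesterone and estrogen metabolites restricted to phase-concordant pairs, using the recorded cycle day. Removing such pairs from the primary test would be harder to defend, since the loss would probably fall mainly on the PCOS patients.

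**Cost.** Time on treatment at follow-up will vary in a few women. With a 3-day window the wait beyond day 84 is 0 days for cycles of 27 to 29 days, 3 for 30, 9 for 32, 17 for 26 (4 × 26 − 3 = 101) and 18 for 35 (3 × 35 − 3 = 102), so up to about two to three weeks. The standardisation for duration in Sections 3.5 and 5 applies to the dose analyses; the primary paired test does not correct for it. Section 3.5 cites 6 weeks at target dosage as enough for a hormonal effect and treats 12 weeks as ample, so the cost is small.
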